# Rationale and design of EXPLORE: a randomized, prospective, multicenter trial investigating the impact of recanalization of a chronic total occlusion on left ventricular function in patients after primary percutaneous coronary intervention for acute ST-elevation myocardial infarction

**DOI:** 10.1186/1745-6215-11-89

**Published:** 2010-09-21

## Abstract

**Background:**

In the setting of primary percutaneous coronary intervention, patients with a chronic total occlusion in a non-infarct related artery were recently identified as a high-risk subgroup. It is unclear whether ST-elevation myocardial infarction patients with a chronic total occlusion in a non-infarct related artery should undergo additional percutaneous coronary intervention of the chronic total occlusion on top of optimal medical therapy shortly after primary percutaneous coronary intervention. Possible beneficial effects include reduction in adverse left ventricular remodeling and preservation of global left ventricular function and improved clinical outcome during future coronary events.

**Methods/Design:**

The Evaluating Xience V and left ventricular function in Percutaneous coronary intervention on occLusiOns afteR ST-Elevation myocardial infarction (EXPLORE) trial is a randomized, prospective, multicenter, two-arm trial with blinded evaluation of endpoints. Three hundred patients after primary percutaneous coronary intervention for ST-elevation myocardial infarction with a chronic total occlusion in a non-infarct related artery are randomized to either elective percutaneous coronary intervention of the chronic total occlusion within seven days or standard medical treatment. When assigned to the invasive arm, an everolimus-eluting coronary stent is used. Primary endpoints are left ventricular ejection fraction and left ventricular end-diastolic volume assessed by cardiac Magnetic Resonance Imaging at four months. Clinical follow-up will continue until five years.

**Discussion:**

The ongoing EXPLORE trial is the first randomized clinical trial powered to investigate whether recanalization of a chronic total occlusion in a non-infarct related artery after primary percutaneous coronary intervention for ST-elevation myocardial infarction results in a better preserved residual left ventricular ejection fraction, reduced end-diastolic volume and enhanced clinical outcome.

**Trial registration:**

trialregister.nl NTR1108.

## Background

Treatment of patients with acute ST-elevation myocardial infarction (STEMI) aims at early restoration of antegrade flow in the infarct related coronary artery in order to preserve myocardial function and improve survival. Angiography after thrombolysis or before primary percutaneous coronary intervention (PCI) has revealed that multivessel disease (MVD) is present in 40-65% of all STEMI patients. These patients are considered to be a subgroup with a high risk for morbidity and mortality, compared with patients with single vessel disease (SVD).[1,2] An aggressive multivessel PCI strategy during and after primary PCI for STEMI has not improved outcome in MVD patients. In fact, studies reported that treatment of non-culprit lesions in STEMI patients with MVD is associated with a higher post-procedural morbidity rate without improving survival.[3-5] In the setting of primary PCI it was recently demonstrated that, the higher mortality in patients with MVD is mainly determined by the presence of a chronic total occlusion (CTO) in a non-infarct related artery (IRA).[6-10] Furthermore, a CTO in a non-IRA was associated with a reduced left ventricular function during hospitalization for the index event and a further reduction in left ventricular function during follow-up.[6] Therefore, STEMI patients with a CTO constitute the MVD patient group with a truly higher risk for death.[6-9] The ongoing Evaluating Xience V and left ventricular function in PCI on occLusiOns afteR STEMI (EXPLORE) trial is the first randomized clinical trial powered to investigate clinical outcome after percutaneous treatment of a CTO. There are two main mechanisms involved in the hypothesis of the Explore trial. First, recanalization of the CTO will possibly restore the contractile function of the hibernating myocardium. Furthermore, recanalization of the CTO might improve the healing of the infarct border zone. This assumption is based on the coronary anatomy where the perfusion area of the infarct related coronary artery and the CTO are adjacent or overlapping. In recently perfused myocardium, the revascularization of a CTO will improve the myocardial perfusion in this overlapping region and therefore might improve the healing of this border zone and might protect against negative remodelling and preserving residual left ventricular function.

The EXPLORE trial will determine whether recanalization of a CTO within one week after primary PCI for STEMI results in a better preserved residual left ventricular ejection fraction and reduced end-diastolic volume.

## Methods/Design

### Overview

The investigator-initiated EXPLORE trial is a prospective, randomized, two-arm trial with blinded evaluation of endpoints. European and North-American high volume primary PCI centers with a 1.5 Tesla cardiovascular magnetic resonance imaging (cMRI) facility participate in this global trial. The study was first approved by the Medical Ethics Committee on human research at the Academic Medical Center-University of Amsterdam, the Netherlands. For all the foreign centers, the study must be approved by the Medical Ethics Committee on human research in each of the corresponding countries before participation. The study will be conducted in accordance with the declaration of Helsinki. The EXPLORE trial was registered on 30-10-2007 at http://www.trialregister.nl with trial ID NTR1108.[11]

After successful primary PCI for STEMI, patients with a CTO in a non-infarct related artery are randomized to either elective PCI of the CTO within seven days after primary PCI or to standard medical treatment. Figure 1 shows the flow chart of the trial.

**Figure 1 F1:**
[figure not shown]
**Flow chart of the EXPLORE trial**. STEMI = ST elevation myocardial infarction PCI = Percutaneous Coronary Intervention CTO = Chronic Total Occlusion

### Patients and Enrolment

Consecutive STEMI patients after successful primary PCI, defined as a residual stenosis of the culprit lesion < 30% and a TIMI flow ≥ 2, are screened for entry into the EXPLORE trial. Patients are suitable for inclusion if coronary angiography preceding the primary PCI reveals at least one CTO, situated in a non-infarct related coronary artery or its side branches. For the purpose of this trial, a CTO is defined as a 100% luminal narrowing without antegrade flow or with antegrade or retrograde filling through collateral vessels. Furthermore, the CTO should be amenable to percutaneous treatment and must be located in a coronary vessel with a reference diameter of at least 2.5 millimeters. All inclusion and exclusion criteria are summarized in Appendix A and B, respectively.

If all inclusion and none of the exclusion criteria are met, the patient is asked for written informed consent, as required by the institutional review board in accordance with the Declaration of Helsinki.

### Randomized Treatment Assignment

After informed consent has been obtained, the local investigator contacts the EXPLORE website http://www.explorerandomization.org for online randomization. Patients are randomly assigned following a computer-generated list in a 1:1 ratio to either PCI of the CTO within seven days after the primary PCI or to standard medical treatment.

### PCI of the CTO(s)

All PCI procedures are performed under the local routine protocols. All angiograms are recorded in such a way that they are suitable for off-line quantitative coronary angiography (QCA). For patients randomized to PCI of the CTO, the procedure is planned as soon as possible after randomization, but at the latest within seven days after the primary PCI. An approved drug eluting stent is used during PCI of the CTO. For the purpose of uniformity in this trial, the investigators intend to use an everolimus eluting stent (EES) in order to study the performance of the EES in this type of lesion with a high risk of restenosis. Routine electrocardiography and blood analysis including cardiac enzymes are performed before and after PCI of the CTO and are repeated at discharge. Patients randomized to this treatment arm receive clopidogrel 75 mg daily or prasugrel 10 mg daily for at least 12 months after drug eluting stent placement [12,13].

### Standard Medical Treatment

In patients randomized to standard medical treatment, the non-infarct related CTO should not be approached invasively during the first four months after randomization. If, however an unequivocal indication for revascularization arises, follow-up cMRI should be performed before CTO intervention.

### Post-STEMI Treatment for Patients with non CTO co-existing coronary lesions

In view of the weak guideline recommendations [14] and the different local practices, our protocol recommends a conservative approach for non-CTO co-existing lesions in the EXPLORE trial. In order to assess the value of CTO revascularization but in view of current daily clinical practice, the decision of the management of non-CTO co-existing lesions must be made before randomization. This decision is made by the local heart team, which generally consist of an interventional cardiologist and or a cardio-thoracic surgeon. In case it is decided that a non-CTO co-existing lesion should be treated, this additional PCI procedure must be performed within one week after the index STEMI. For patients randomized to recanalize the CTO, this additional PCI procedure will be performed during the same procedure as the CTO lesion is being treated. For patients in the conservative group, this additional PCI for non-CTO co-existing lesions will be scheduled within one week after the index STEMI. After the first week, revascularization is only indicated when clinically and or ischemia driven and is preferably performed after four months.

### Post-STEMI Treatment for all Patients

All patients included in this trial are treated according to the current ACC/AHA guidelines regarding post STEMI management specifying treatment with at least 100 mg of aspirin daily, clopidogrel in a dosage of at least 75 mg daily or prasugrel 10 mg daily for at least 12 month after primary PCI, adequate lipid-lowering medication, angiotensin converting enzyme (ACE) inhibitors, and beta-blockers.[12,13]

### Follow-up

All patients visit the outpatient clinic at 30 days, four months, and twelve months after primary PCI. Thereafter, patients will be followed-up by means of a telephone call at two, three, four, and five years. During all three follow-up outpatient clinic visits, clinical evaluation with a 12-lead electrocardiogram and an inventory of adverse events is obtained. Adverse events included in this inventory are cardiac and non-cardiac death, stent thrombosis according to the definition of the Academic Research Consortium (ARC)[15] myocardial re-infarction, all cardiac surgery, implantation of an implantable cardioverter-defibrillator device, clinically overt heart failure, repeat coronary angiography and repeat PCI, hospital admission for angina, stroke, and severe bleeding events.

At four months, cMRI is performed in all patients along with routine laboratory measurements and exercise testing. If a contraindication for cMRI has risen because of altered patient characteristics after inclusion, the protocol permits single positron emission computed tomography (SPECT) as a secondary and echocardiography as a tertiary modality for endpoint assessment.

Scheduling of repeat angiography is at the discretion of the treating physician. Repeat angiography is preferably performed at one year after randomization in all patients.

### Cardiac Magnetic Resonance Imaging

After written informed consent, baseline cMRI is recommended to be performed at least 48 hours after the primary PCI but before the patient is randomly assigned to one of the treatment arms. All patients undergo cMRI at four-month follow-up to assess the primary endpoints of this trial. Patients are studied on a clinical 1.5-Tesla scanner using a 4-element phased array cardiac receiver coil. For functional imaging, electrocardiogram-gated cine steady-state, free-precession magnetic resonance images are obtained during repeated breath holds in the 3 standard long-axis views (4 -, 3- and 2-chamber view). Additional short-axis slices are acquired, covering the entire left ventricle from base to apex, to examine regional and global left ventricular function. Late contrast-enhanced (LCE) images are acquired 10 minutes after administration of a gadolinium-based contrast agent with an inversion recovery, gradient-echo pulse sequence to identify the location and extent of myocardial infarction. The data are obtained with slice locations identical to the functional images. All MRI images are sent to an independent core laboratory for quality control and blinded central analysis. On the short axis cine slices, the endocardial and epicardial borders are outlined manually in end-diastolic and end-systolic images, excluding trabeculae and papillary muscles. Assessment of global left ventricular function is obtained by calculating left ventricular volumes, mass, and ejection fraction using the summation of slice method multiplied by slice distance.

### Primary Endpoints

The two primary endpoints of this trial are differences between the two treatment arms in left ventricular ejection fraction (LVEF) and left ventricular end-diastolic volume (LVEDV), assessed by cMRI at four months after primary PCI for STEMI, Appendix C.

### Safety and Other Secondary Endpoints

Safety will be determined by the assessment of Major Adverse Coronary Events (MACE) defined as cardiac death, peri-procedural myocardial infarction, myocardial infarction or any repeat coronary intervention at 30 days, 4 months and 1, 2, 3, 4, 5 years. Furthermore, safety is also determined by the occurrence of stent thrombosis. All safety endpoints are defined in accordance with the ARC [15]. The trial will be monitored by a Data and Safety Monitoring Board (DSMB) and the trial will be discontinued in case of safety concerns.

All other secondary endpoints are displayed in Appendix C.

A pre-specified subgroup analysis will be performed in which the primary outcome, Major Adverse Coronary Events (MACE) and suitable other secondary endpoints will be stratified according to the presence of non-CTO co-existing lesions.

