### PCI of a CTO: higher risk of restenosis

Percutaneous recanalization of a CTO amenable to PCI treatment can be performed with a success rate of 70-80%, but is associated with a higher rate of restenosis compared to PCI of non-occluded vessels. Although coronary stenting has been shown to be superior to conventional balloon angioplasty, restenosis rates remain relatively high. When compared to bare metal stents, drug eluting stents (DES) are effective in decreasing the need for repeat intervention in successfully treated CTO patients.[27] However, there have been concerns about long-term delay of arterial healing as a consequence of both Sirolimus eluting stent (SES) and Paclitaxel eluting stent (PES) placement and the associated risk of late stent thrombosis. Both preclinical and clinical data for a second-generation DES, the EES, are encouraging in terms of arterial healing and low restenosis rates. The EES showed superior endothelialization compared with the PES, SES and Zotarolimus-eluting stent at 14 days after stent implantation.[28] This suggests a superior safety profile for the EES, as shown in the one-year results of the SPIRIT IV trial, randomizing 3687 patients in a 2:1 fashion to either the EES or the PES for treatment of patients with de novo coronary artery disease with a maximum of 3 lesions. The SPIRIT IV investigators reported a 0.29% ARC definite or probable stent thrombosis rate in the EES arm, as compared to 1.1% in the PES arm (p = 0.003). Furthermore, the EES performed superior over the PES regarding ischemia-driven target lesion revascularization, (3.9% vs 6.6%, p = 0.0008).[29] Although extensively studied in relatively low-risk lesions, currently data regarding the performance of the EES in CTO's are lacking.

To conclude, no clinical trial to date has investigated the effect of percutaneous recanalization of CTO's on clinical endpoints in any setting. The high case-fatality rates and inferior recovery of LV function after STEMI of patients with a CTO in a non-IRA provide the rationale for the current trial. The ongoing EXPLORE trial is the first randomized clinical trial powered to investigate clinical outcome after percutaneous treatment of a CTO. The Explore trial will determine whether recanalization of a CTO within one week after primary PCI for STEMI results in a better preserved residual left ventricular ejection fraction and reduced end-diastolic volume.

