## Appendix A

### Inclusion criteria EXPLORE trial

Patients are eligible for inclusion if all of the inclusion criteria are met:

- Successful primary percutaneous coronary intervention^1 ^for acute ST elevation myocardial infarction^2^

And

- Presence of at least one chronic total occlusion located in a non-infarct related coronary artery, defined as a 100% luminal narrowing without antegrade flow or with antegrade or retrograde filling through collateral vessels

And

- Reference diameter of ≥2.5 millimeters

And

- Amenable to treatment by percutaneous coronary intervention

1 Residual stenosis of the culprit lesion < 30% and Thrombolysis In Myocardial Infarction flow ≥ 2.

2 definition according to Alpert et al. Myocardial infarction redefined - a consensus document of The joint ESC/ACC committee for the redefinition of myocardial infarction [30].

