### Secondary Endpoints

#### Safety Endpoints

Major Adverse Cardiac Events, defined as cardiac death, myocardial infarction or any repeat coronary

intervention* at 30 days, 4 months, and 1, 2, 3, 4, and 5 years

Stent thrombosis, classified as definite, probable or possible

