#### Other Secondary Endpoints

Measured by cardiac magnetic resonance imaging at 4 months:

- Left ventricular end-systolic volume - Left ventricular segmental wall thickening

- Left ventricular mass - Infarct size (by late contrast enhancement)

N Terminal - pro Brain Natriuretic Peptide (at 4 months and 1 year, relative to baseline)

Heart rate-adjusted QT (QTc) duration measured by resting electrocardiography (at 4 months and 1 year, relative to baseline)

Quantitative Coronary Angiography of the treated chronic total occlusions:

- in-stent and in-segment late luminal loss at 12 months

- in-stent and in-segment minimal luminal diameter

- in-stent and in-segment binary restenosis rate

Repeat Hospitalization for cardiac causes at 30 days, 4 months, and 1, 2, 3, 4, and 5 years

Presence of clinically overt heart failure at 30 days, 4 months, and 1, 2, 3, 4, and 5 years

Implantation of implantable cardioverter-defibrillator devices

Functional Class: NYHA classification at 30 days, 4 months, and 1, 2, 3, 4, and 5 years

*Excluding the initial percutaneous coronary intervention of the chronic total occlusion when randomly

assigned to this treatment arm. MRI: Magnetic resonance imaging NYHA: New York Heart Association

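### MACE exempts only the first CTO PCI, so first-week procedures the protocol itself directs are counted differently in the two arms; the net direction is unknown

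*Protocol article*

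**What the plan says.** Protocol article, Safety and Other Secondary Endpoints: safety is judged by MACE, whose last components are "myocardial infarction or any repeat coronary intervention at 30 days, 4 months and 1, 2, 3, 4, 5 years". No exemption is given there. Appendix C, Safety Endpoints, repeats the definition ("Major Adverse Cardiac Events, defined as cardiac death, myocardial infarction or any repeat coronary" intervention), omits peri-procedural infarction, and adds an asterisk. The footnote, printed under Other Secondary Endpoints, reads "Excluding the initial percutaneous coronary intervention of the chronic total occlusion when randomly" assigned to that arm. It is the only exemption in the article.

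Four other statements bear on who can have a further procedure:

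- **Number of occlusions.** Appendix A requires "Presence of at least one chronic total occlusion located in a non-infarct related coronary artery", and Patients and Enrolment likewise says that angiography "reveals at least one CTO, situated in a non-infarct related coronary artery or its side branches". More than one CTO is therefore allowed.
- **Success of CTO PCI.** Statistical Considerations assumes 80%. The Discussion says the procedure "can be performed with a success rate of 70-80" percent.
- **CTO PCI in the control arm.** Under Standard Medical Treatment the CTO "should not be approached invasively during the first four months after randomization", with an exception for an unequivocal indication, after follow-up cMRI.
- **Planned PCI of non-CTO lesions.** The decision is made before randomization. The CTO arm has this PCI in the same session as the CTO. The control arm has it as a procedure of its own within a week of the index STEMI.

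**The concern.** A repeat intervention should score as an adverse outcome when something has gone wrong or recurred. It should not score because the protocol's own treatment took two visits. The exemption is meant to make that separation, but it is worded for one session in one arm. Some procedures that only deliver the strategy chosen at or before randomization fall outside it, and which ones do so depends on the arm.

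At stake is the early safety comparison (30 days and four months). The article says safety will be determined by MACE and stent thrombosis, that a safety board monitors the trial, and that the trial will be discontinued if safety concerns arise. The events committee adjudicates MACE as the protocol specifies, so the wording governs the count.

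**Working it through.** **1. What the wording counts.** The repeat-intervention component could be read as covering only a lesion treated before. The footnote rules that reading out: the first CTO PCI treats a lesion not yet treated in the trial, and it would need no exemption unless procedures after the primary PCI counted in general. On that basis:

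| First-week procedure | CTO arm | Control arm |
|---|---|---|
| First CTO PCI | exempt | should not occur, apart from the exception |
| Second CTO session (second CTO, or early second attempt) | counts | almost no counterpart |
| Planned non-CTO PCI | inside the exempt session, no separate event | separate procedure, counts |

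Row 2 works against the CTO arm and row 3 against the control arm. For a second CTO in a second session, the footnote could be read per patient (counts) or per lesion (exempt). A second attempt on the same CTO is not initial on either reading.

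**2. Inputs.** From the article: 150 per arm and 80% CTO success, hence 0.20 × 150 = 30 expected failures. The article states no MACE rate, so there is no figure of its own to reproduce. Assumed:

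- b = background MACE risk, 10% (5% as an alternative).
- s = share of CTO-arm patients with an unexempted further CTO session.
- q = share of control patients with a planned first-week non-CTO PCI, 0 to 20%.

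Scale for s, from assumed rates:

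- Second CTO in 5-15% of patients, staged in 25-50% of those: 150 × 0.05 × 0.25 = 1.9 to 150 × 0.15 × 0.50 = 11.3 patients, about 1.3% to 7.5%.
- Re-attempts in 10%, 25% or 50% of the 30 failures: 3, 7.5 or 15 patients, or 2%, 5% or 10%. These may fall at any time, and only some would be in the first week.

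**3. Formula.** Expected events are 150 × [1 - (1 - b)(1 - s)] in the CTO arm and 150 × [1 - (1 - b)(1 - q)] in the control arm. The difference in risk is (1 - b)(s - q).

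**4. Results at b = 10%.**

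| s | q | CTO arm | Control arm | Difference (points) |
|---|---|---|---|---|
| 5% | 0 | 21.75 | 15 | +4.5 |
| 10% | 0 | 28.5 | 15 | +9.0 |
| 5% | 5% | 21.75 | 21.75 | 0 |
| 5% | 10% | 21.75 | 28.5 | -4.5 |
| 5% | 20% | 21.75 | 42 | -13.5 |
| 0 | 5% | 15 | 21.75 | -4.5 |
| 0 | 10% | 15 | 28.5 | -9.0 |

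The two effects cancel when s = q, and the sign turns when q exceeds s. The last two rows also show what happens if only the extra CTO sessions are exempted: the control arm stays penalised.

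**5. Chance of a spurious significant result.** This takes the CTO-arm effect alone (q = 0), with no true difference and a two-sided Fisher test at 0.05:

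| Added share s | b = 10% | b = 5% |
|---|---|---|
| 0 | 3.3% | 2.4% |
| 3.3% | about 10% | about 13-14% |
| 5% | 17.6% | 27.3% |
| 8% | 38.5% | 58.2% |

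The 3.3% row matches the low ends in step 2 (about 2 + 3 = 5 patients of 150). The article names a Cox model for MACE, so these figures show scale and are not the planned test.

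**The case against.** The strongest reply has five parts.

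- **Staging and second attempts are not in the protocol.** It speaks of one procedure within seven days. With baseline cMRI recommended at least 48 hours after primary PCI and before randomization, about five days remain for two sessions. This stands as a limit on size. It does not remove the problem, since several CTOs are allowed and a second session is not excluded.
- **A re-attempt after a failed CTO PCI is a real burden of the invasive strategy.** This stands for later re-attempts: counting them is defensible, and exempting them could hide harm.
- **Appendix C governs.** Statistical Considerations refers to it for all secondary endpoints, so the missing exemption in the main text may be harmless. This is largely right, but the footnote is still too narrow.
- **MACE is secondary and centrally adjudicated, and a condensed article may leave such detail to the full protocol.** This is partly right. But the article does state an exemption, and the stated one treats the arms differently.
- **The safety board sees more than MACE.** This is true: it also reviews serious adverse events, device effects and failures, and protocol deviations.

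A reader might infer that early MACE is inflated against CTO PCI. The documents do not support that, because the planned non-CTO PCI in the control arm pulls the other way in the same week and neither rate is given. Nor is the control arm barred from CTO PCI: the text discourages it and allows an exception.

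**Conclusion.** The point holds as one of asymmetric counting. Under the literal wording, a further first-week CTO session scores only in the CTO arm, and planned first-week non-CTO PCI scores only in the control arm. The second half rests on reading a PCI done within the exempt session as no separate event.

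Direction and size cannot be determined. The illustrations run from +9.0 to -13.5 points at an assumed 10% background rate, with exact cancellation in between. Such cancellation would be chance, in different patients, and would not make the endpoint sound. The effect may also be small: with 3.3% added in the CTO arm alone, the chance of a significant result is about 10-14%.

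The 30-day and four-month readouts are the most exposed, but these events also carry into later cumulative MACE. The co-primary LVEF and LVEDV analyses are not touched. The change is worth making, but the trial's main conclusion does not depend on it.

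**What to change.** Reconcile the section on non-CTO co-existing lesions, the MACE definition in Safety and Other Secondary Endpoints, and Appendix C with its footnote, so that one definition applies throughout:

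- In both arms, exclude from the repeat-intervention component every PCI session that delivers the assigned treatment, or treatment planned before randomization, within the protocol's first-week window.
- Continue to count death, infarction and stent thrombosis arising from any session, including excluded ones.
- Keep later CTO re-attempts in MACE, but report them as a separate component.
- Show MACE with and without the intervention component.

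Both exclusions must be made together. Exempting only the extra CTO sessions leaves the control arm penalised (15 v 21.75 expected events at q = 5%).

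The cost is a short endpoint amendment and an instruction to the events committee, with no new data. The downside is that first-week second sessions no longer appear in MACE, so their number must be reported separately by arm.
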